**Table 11.3.1.3. Causality assessment of AEs and study drugs**

| Criteria | Definition |
| --- | --- |
| Definitely | The administration time and onset of the event exhibit a reasonable relationship, the suspected AEs fulfill the criteria for the typical reactions of the drug, the suspected AEs disappear or are mitigated after drug discontinuation, and the same AEs recurred after repetitive administration of the study drugs. |
| Probably | The administration time and onset of the event exhibit a reasonable relationship, a clinical course not consistent with the known effects, and the clinical status of the patient and other modalities may also produce the event. |
| Possibly | The event does not follow a sequence of time from drug administration, is not a previously known or suspected effect of the test drug, and the clinical status of the patient and other modalities may also produce the event. |
| Unlikely | The event does not follow a sequence of time from drug administration, is not a previously known or suspected effect of the test drug, the clinical status of the patient and other modalities may produce the event, the suspected AEs disappear or are mitigated after drug discontinuation, and the same AEs recurred after repetitive administration of the study drugs. |
| Unrelated | No clear relationship between the onset of the event and the administration time, a clinical course is consistent with the known effects, and other concomitant drug uses that may also produce the event |

- - 1. **SAEs**
       1. **Definitions of SAEs**

SAE is defined as any adverse event that results in any one of the following unanticipated events during the clinical trial period:

(1) Life-threatening events (immediate risk of death);

(2) Resulting in hospitalization or prolongation of existing hospitalization;

(3) Causing persistent or severe disability or incapacity;

(4) Causing congenital anomalies/birth defects;

(5) Drug overdose.

- - - 1. **Pregnancy**

Pregnancy in patients will be reported as SAEs.

- - - 1. **Disease progression**

Disease progression (including signs and symptoms of progression) under the trial will not be reported as SAEs, but death due to disease progression during the trial or safety reporting period will be reported as SAEs. Hospitalization due to signs and symptoms of disease progression will also not be reported as SAEs. During the trial or safety reporting period, events leading to death must be reported as SAEs.

- - - 1. **Undergo other anti-tumor treatments**

If the subject initiates other anti-tumor therapy, the AEs do not result in death are reported until the initiation of a new antineoplastic therapy. If death occurs within the entire SAE reporting period after the end of the study treatment, death must be reported regardless of whether the patient received additional treatment.

- - - 1. **Hospitalization**

AEs in clinical settings resulting in hospitalization or prolongation of existing hospitalization should be considered SAEs. Any initial admission (even if less than 24 hours) to a healthcare facility meets this criterion. Hospitalization excludes the following.

1. Rehabilitation facility;
2. Nursing facility;
3. Routine emergency room admissions;
4. Same-day surgeries (as outpatient/same-day/ambulatory procedures).

If hospitalization or prolongation of hospitalization does not result from worsening AEs, the AEs will not be reported as SAEs. Including:

1. Admission for treatment of a preexisting condition not associated with the development of a new AE or with a worsening of the preexisting condition (e.g., for work-up of persistent pre-treatment lab abnormality);
2. Administrative admission (e.g., for the yearly physical exam);
3. Protocol-specified admission during a clinical trial (e.g., for a procedure required by the trial protocol);
4. Optional admission not associated with a precipitating clinical adverse event (e.g., for elective cosmetic surgery);
5. Pre-planned treatments or surgical procedures should be noted in the baseline documentation for the entire protocol and/or for the individual subject;
6. Admission exclusively for the administration of blood products.

Diagnostic and therapeutic non-invasive and invasive procedures, such as surgery, should not be reported as AEs. However, the medical condition for which the procedure was performed should be reported and it meets the definition of AEs. For example, acute appendicitis that begins during the AEs reporting period should be reported as AEs, and the resulting appendectomy should be recorded as treatment of the AEs.

- - - 1. **SAEs reporting requirements**

SAEs should be reported from the date the subject signs the informed consent until 30 (inclusive) calendar days after the last dose of the study drug. If an SAE occurs, the clinical monitor and principal investigator are to be notified within 24 hours of awareness of the event. Meanwhile, fill out, sign and date the SAE form, and immediately report it by fax to the sponsor, the team leader, the ethics committee, the SFDA, and the FDA of the (province or city) of the researcher's region.

SAEs should be reported to the sponsor within 24 hours during a period of continued administration of drugs after the end of the study. Information on all SAEs is required to be recorded in the SAE form. SAEs occurring within 30 days of the last dose must be reported and occurring after 30 days of the last dose are generally not reported unless suspected to be related to the study drug.

SAEs should be recorded faithfully, together with the time of occurrence, severity, duration, management, and outcomes. If the investigator considers that an SAE is unrelated to the study drug but is potentially related to the clinical process (e.g., discontinuation of treatment, or comorbidity during the trial), this relationship should be detailed in the narrative section of the SAEs page of the CRF. If any changes are made to the grade of SAEs and the causality to study drugs during the study, changes must be reported to the sponsor. All SAEs should be followed up until recovery or stabilization of the disease.

- - - 1. **SAEs reporting procedures**

Any SAE occurring during the clinical period and within 30 days after discontinuation of the drug must be reported immediately to the CRA of the sponsor, the PI of the clinical study unit, and the ethics committee, as well as, report to the State Food and Drug Administration Drug Registration Division, safety supervision department, and Health administrative department, respectively, within 24 hours. Meanwhile, the investigator must complete an SAE Form with a detailed description of the time of SAE occurred, its severity, its causality to study drugs, and the interventions performed, and sign the report.

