An AE is any unintended medical occurrence in a clinical study after the signing of informed consent, which does not necessarily have a causal relationship with the treatment, regardless of whether it is assigned to the experimental groups or even the administration of drugs. Any abnormal changes in objective laboratory tests should be recorded faithfully, together with the time of occurrence, severity, duration, management, and outcomes. Relationships between the study drug and AEs were rated by the investigator as definitely, probably, possibly, unlikely, and unrelated according to five criteria. Definitely, probably, and possibly are classified as drug-related AEs and the incidence of AEs is calculated using the above three as the numerator and the total number of subjects in the safety assessment set as the denominator. The criteria of causality assessment are as follows.

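### The causality table counts 'Possibly' as drug-related but drops the same event to 'Unlikely' once it resolves on stopping and recurs on re-exposure, so the drug-related AE incidence is not reliable as defined

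*Protocol*

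**What the plan says.** Protocol section 10.2, under the heading on causality to study drugs, has the investigator place each AE in one of five categories. It then sets the cut: "Definitely, probably, and possibly are classified as drug-related AEs". The rate is "calculated using the above three as the numerator and the total number of subjects in the safety assessment set as the denominator". Unlikely and Unrelated are therefore outside the numerator.

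Table 11.3.1.3 defines the categories:

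- **Definitely** (counted): reasonable timing; "the suspected AEs fulfill the criteria for the typical reactions of the drug"; resolution or easing on stopping; and "the same AEs recurred after repetitive administration of the study drugs".
- **Probably** (counted): reasonable timing, a course that does not fit the known effects, and other causes that may contribute.
- **Possibly** (counted): "The event does not follow a sequence of time from drug administration, is not a previously known or suspected effect of the test drug", and other causes may contribute.
- **Unlikely** (not counted): opens with the same words as Possibly, then "the clinical status of the patient and other modalities may produce the event, the suspected AEs disappear or are mitigated after drug discontinuation", and again "the same AEs recurred after repetitive administration of the study drugs".
- **Unrelated** (not counted): no clear time relation, "a clinical course is consistent with the known effects", and other concomitant drugs that may explain the event.

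No other part of the protocol gives a second causality table or corrects this one.

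**The concern.** In a causality scale, each added piece of evidence for the drug should hold the rating or raise it. Here two pieces that help to lift an event to Definitely are also what separates Unlikely from Possibly, and there they lower the rating. The reversal falls exactly on the line between counted and not counted.

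The consistency criterion also looks misplaced. A course out of line with the drug's known effects is required for Probably, while a course in line with known effects appears under Unrelated.

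At stake is the drug-related AE incidence, which section 10.2 defines directly from these rows. Investigators code from this table, and the protocol fixes both the definitions and the numerator. A later analysis plan could not repair the coding by choosing a different summary method.

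**Working it through.** The plan states no expected drug-related rate, so there is no figure to reproduce. The check compares the rows element by element.

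**Step 1. The rows of Table 11.3.1.3 against the cut in section 10.2**

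| Row | Counted | Timing | Known effect | Other cause | Resolves on stopping | Recurs on re-administration |
|---|---|---|---|---|---|---|
| Definitely | yes | reasonable | typical reaction | not mentioned | yes | yes |
| Probably | yes | reasonable | course does not fit | may contribute | not mentioned | not mentioned |
| Possibly | yes | no sequence | not known or suspected | may contribute | not mentioned | not mentioned |
| Unlikely | no | no sequence | not known or suspected | may contribute | yes | yes |
| Unrelated | no | no clear relation | course fits (effects of what is not said) | concomitant drugs | not mentioned | not mentioned |

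**Step 2. Unlikely minus Possibly.** The first three elements cancel. What remains is positive dechallenge and positive rechallenge. An event with no time sequence and no known link is counted. The same event with dechallenge and rechallenge evidence is not.

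**Step 3. A known effect, reasonable timing, drug continued.** Table 7.4.1 continues anlotinib for grade I and II hypertension, and Table 7.4.3 does so for grade 1 and 2 proteinuria. The cleanest cases are grade II hypertension, because section 7.4 records hypertension as an AE only from grade II, and grade 1 proteinuria, because the running text of section 7.4 treats grade 2 proteinuria differently from Table 7.4.3. Try each row:

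- Definitely fails: the drug was not stopped and restarted.
- Probably fails: the course does fit the known effects.
- Possibly and Unlikely fail: the event is a known effect and follows dosing.
- Unrelated fails: there is a time relation.

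Read literally, the event fits no row, and so no counted row.

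**Step 4. The same event with the drug stopped but not restarted.** Positive dechallenge without rechallenge still fails Definitely, and the other rows fail as in step 3. This is a second gap.

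**Step 5. Direction.** Counting events with no time relation as Possibly pushes the rate up. Dropping dechallenge- and rechallenge-positive events to Unlikely, and leaving known effects without a counted row, pushes it down. The net sign cannot be derived.

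**Step 6. Scale only.** Section 3.3 plans at least 155 subjects per group. Assume a safety set of about 155 per arm and a rate counted per subject. If k subjects are misclassified on their only drug-related event, the arm's rate moves by k/155:

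- k = 1: 1/155 = 0.65 percentage points
- k = 5: 5/155 = 3.2 percentage points
- k = 10: 10/155 = 6.5 percentage points

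These values of k are illustrations, not estimates.

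**The case against.** The strongest reply is that few real events can meet the Unlikely row. It needs all its elements together, and an event with no time sequence that still resolves on stopping and recurs on re-exposure comes close to contradicting itself. Investigators also rate causality by judgement, and the protocol reads as a translation, so the text used at sites may be better ordered. All of this is fair. It limits how often the inversion bites, but it does not correct the text shown, and it does not touch the gaps in steps 3 and 4, which concern ordinary events.

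Several stronger readings are tempting, and the protocol does not support them:

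- *Hand-foot reaction or raised blood pressure that returns on re-exposure would be coded Unlikely.* It would not. Both are known effects in this protocol, so they fail that row. With reasonable timing, resolution and recurrence they meet Definitely and are counted.
- *Typical drug effects would be coded Unrelated.* That row also needs no clear time relation and a concomitant drug as explanation. Its phrase on known effects does not say effects of what, and may mean those of the concomitant drugs. The wording is ambiguous rather than plainly reversed.
- *The safety signal to the IDMC is wrong.* Section 13.3 says only that the committee analyses safety and efficacy data. It does not tie the committee to drug-related rates.
- *The safety comparison between arms is compromised.* The synopsis and section 13.2 already summarise and compare all AEs, those of grade 3 or above, and serious events, with no causality filter.

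**Conclusion.** The point holds for one quantity. The drug-related AE incidence of section 10.2 is not reliable as defined, for two reasons. Possibly and Unlikely are inverted at the counting boundary, and the Probably wording leaves common known effects without a counted category. The Unrelated wording is at best ambiguous.

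It would go too far to say that the rate will be wrong by some amount. Size and net direction depend on how sites applied the table, which the protocol cannot show. The 0.65 points per misclassified subject rests on an assumed safety set of about 155 per arm and a per-subject rate.

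The primary endpoint and the all-causality, grade 3 or above and serious AE summaries are unaffected. The table should be corrected because a stated rule gives a wrong classification and the correction is cheap. The design itself is not in question.

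**What to change.** Reorder Table 11.3.1.3 so that reasonable timing, consistency with the drug's known effects, and positive dechallenge or rechallenge support only the counted categories. Specifically:

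- Remove dechallenge and rechallenge from Unlikely.
- Correct the Probably row so that a course in line with the known effects supports it.
- State in the Unrelated row whose known effects are meant.
- Make the five rows cover all cases, including a known effect with reasonable timing where the drug was continued, or was stopped and not restarted.

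Issue the corrected table to sites and re-review causality already coded, with treatment still masked, before the drug-related incidence is tabulated. No change to the all-causality comparisons is needed.

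The cost is one table, one site memo and a re-review of one field. No new data are required: section 10.2 already has investigators record onset, duration, severity, management and outcome for each event.

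### The SAE definition covers only unanticipated outcomes and omits death, so it contradicts the paragraphs after it and leaves a narrow gap for expected life-threatening or disabling toxicities

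*Protocol*

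**What the plan says.** All of the relevant SAE text is in Protocol section 10.2, under the SAE headings.

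- **Definitions of SAEs.** "SAE is defined as any adverse event that results in any one of the following unanticipated events". Five numbered outcomes follow: life-threatening events, hospitalisation or its prolongation, lasting or severe disability, congenital anomaly, and overdose. Death is not among them.
- **Disease progression.** Progression itself is not an SAE, but "death due to disease progression during the trial or safety reporting period will be reported as SAEs". The paragraph ends with a general rule that "events leading to death must be reported as SAEs".
- **Hospitalization.** "AEs in clinical settings resulting in hospitalization or prolongation of existing hospitalization should be considered SAEs". A stay of under 24 hours counts. Some admissions are excluded.
- **SAEs reporting requirements.** "If an SAE occurs, the clinical monitor and principal investigator are to be notified within 24 hours of awareness of the event".

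Section 13.2, under safety analysis, then compares three groups of events between the arms: all AEs, TEAEs of grade 3 or more, and serious TEAEs.

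**The concern.** Seriousness describes what an event did to the patient. Expectedness describes whether the event was foreseen. The opening sentence merges the two, because its qualifier governs every item on the list. The paragraphs after it then treat deaths and admissions as serious whether or not they were foreseen. A site that works from the definition and a site that works from the later paragraphs can classify the same event differently.

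Two things depend on the classification: the 24-hour notification, and the serious-TEAE row of the between-arm safety table. The toxicities the protocol foresees are largely those of anlotinib. If the qualifier were applied literally, any events lost from the serious count would therefore tend to come from the experimental arm.

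**Working it through.** No arithmetic applies. The check sets the definition beside the later SAE paragraphs and asks how an *expected* event is classified for each outcome.

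| Outcome | In the numbered list | Later text without an expectedness condition | Expected event, read literally |
|---|---|---|---|
| Death | No | Yes (Disease progression) | SAE; definition and later text disagree |
| Hospitalisation or prolongation | Yes, if unanticipated | Yes (Hospitalization), with exclusions | SAE in most cases; definition and later text disagree |
| Life-threatening | Yes, if unanticipated | None | Not an SAE unless also fatal or admitted |
| Lasting or severe disability | Yes, if unanticipated | None | Not an SAE unless also fatal or admitted |
| Congenital anomaly | Yes, if unanticipated | Not directly, but a patient's pregnancy is itself an SAE | Little practical effect |
| Overdose | Yes, if unanticipated | None | Expectedness hardly applies |

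Of the five listed outcomes, none is death, and one (hospitalisation) is restated later without the qualifier. The gap that matters is in the life-threatening and disability rows.

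**Does the protocol foresee such events?** Yes.
- Section 7.2 has rules for grade IV haematological and non-haematological toxicity.
- Table 7.4.1 lists grade IV hypertension and describes it as life-threatening.
- Section 7.4 has entries for grade 3–4 bleeding, arterial thrombosis including stroke and myocardial infarction, grade IV venous thrombosis, posterior leukoencephalopathy and gastrointestinal perforation.

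**Does the hospitalisation rule catch them all?** Not all. It leaves out routine emergency-room attendance, same-day outpatient surgery and admission solely for blood products. An expected grade IV event handled in one of those ways misses the hospitalisation route. Read literally, it also misses the life-threatening route, because it was foreseen.

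**Where does such an event end up?** It need not be notified within 24 hours and need not be counted as a serious TEAE. It is still recorded as an AE. On the severity scale in section 10.2, grade IV is life-threatening and grade III includes disabling events, so it also enters the comparison of TEAEs of grade 3 or more.

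**The case against.** The best defence is that the section should be read as a whole. The specific rules on death and hospitalisation govern those outcomes, and they set no expectedness condition. The qualifier may also be loose wording. Grammatically it attaches to the outcome rather than to the drug's known effects. The SAE section offers no reference list against which to judge expectedness, and the report asks for timing, severity, causality and interventions only. In section 1.1 the investigators call a case of hypertension in their earlier apatinib–gefitinib study a drug-related SAE, which suggests that they do not use the term restrictively.

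Much of this stands, and it rules out three stronger readings that a reader might infer.

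- *That admissions or deaths from expected toxicities escape SAE reporting.* The later paragraphs make fatal events and AE-related admissions SAEs. For these outcomes the fault is a contradiction between passages, not an uncovered gap.
- *That the 13.2% rate of grade 3–5 hypertension quoted in section 1.1 indicates the scale.* That figure measures severity, not seriousness. Table 7.4.1 sets grade III hypertension by a blood-pressure reading, which does not by itself meet any SAE criterion.
- *That the between-arm safety comparison is shown to be biased.* A direction can be argued, but no rate supports a size. Events of grade 3 or more are compared in any case, and section 13.3 gives the IDMC safety data without limiting it to SAE counts.

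The defence does not reach life-threatening or disabling events. That the qualifier is only loose wording is an inference. Nothing in the protocol says so, and in a multicentre trial sites may apply the sentence as printed.

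**Conclusion.** The definition is wrong as written, with a limited effect. It makes seriousness depend on expectedness, omits death, and contradicts its own later paragraphs. Those paragraphs restore deaths and most hospitalisations. What remains is an expected anlotinib toxicity that is life-threatening or disabling without death or a qualifying admission.

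The number of such events cannot be estimated, because the protocol gives no SAE rate for the combination. It is probably small, since most events of that severity would lead to an admission that counts; this is a judgement, not a figure from the document. The conclusion assumes that sites apply the sentence literally. That these events stay in the grade 3 or higher table assumes that the section's general severity scale, offered for events not listed in CTCAE, also describes the listed ones. That table limits the loss to the analysis, but it does not trigger a 24-hour report. The PFS analysis is unaffected.

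**What to change.** 1. Delete the word unanticipated from the opening sentence of Definitions of SAEs.
2. Add death to the numbered list, so that the definition agrees with the paragraphs on disease progression and hospitalisation.
3. Record expectedness as a separate attribute of the SAE report, with no bearing on whether the event is serious.

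If events have already been classified under the present wording, check the recorded grade IV and disabling AEs against the corrected definition before database lock.

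The cost is a wording change to the protocol and the SAE form guidance, one listing review if events have already been classified, and slightly more SAE reports.
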